## Abstract

**Introduction:**

The effect of Yiqi Fumai lyophilized injection (YQFM) on acute heart failure (AHF) patients has been evaluated in a large sample, randomized, controlled trial (AUGUST-AHF RCT study). However, restrictive eligibility criteria from a randomized clinical trial may raise concerns about the generalizability of the results to under-represented groups or complex patients with multimorbidity. Therefore, we intend to conduct the AUGUST-AHF cohort study which aims to assess the effectiveness of YQFM in patients with AHF in a real-world setting and compare the results with AUGUST-AHF RCT study.

**Methods and analysis:**

This prospective, multicenter cohort study will be conducted at 50 secondary and tertiary hospitals in China and comprise 1,200 patients with AHF. The participants will be followed for up to at least 180 days. The primary outcome is a composite of 90-day all-cause mortality or readmission for heart failure. The secondary outcomes include length of hospital stay, cardiac-specific death, MACE, NYHA cardiac function classification. Cox proportional-hazards regression models will be used to estimate the association between YQFM use and the primary outcome. The primary analysis will use propensity-score matching methods to balance the differences in baseline variables between treatment cohorts.

**Ethics and dissemination:**

Approval for the study has been obtained from the Ethical Committee of Dongzhimen Hospital (approval No. 2022DZMEC-327-02) and registered at ClinicalTrials.gov (NCT05586048). The study results will be published in peer-reviewed journals and presented at scientific conferences.

## 1. Introduction

Acute heart failure (AHF) occurs when the systemic circulatory system fails due to structural or functional heart abnormalities that are severe enough to necessitate hospitalization or emergency department visits (1). Once hospitalized, about 45% of AHF patients will be re-hospitalized or die within one year, imposing a heavy burden on patients and national healthcare systems worldwide (2, 3). During hospitalization, the pharmacological treatment for AHF consists primarily of intravenous diuretics with adjunctive vasodilators, inotropes, or vasopressors, which has minimal efficacy in improving post-discharge outcomes (1, 4). SGLT2 inhibitor empagliflozin has been preliminarily proven to have a long-term mortality benefit on AHF patients in recent months (5); nevertheless, their use remains limited in clinical practice due to cost, side-effect, and lack of availability in local pharmacies (6, 7).

In China, traditional Chinese medicine (TCM) has been widely used in the treatment of heart disease for thousands of years. Yiqi Fumai lyophilized injection (YQFM) is an injection from Chinese medicine extraction processed by modern technology and is derived from the ancient formula Shengmai powder composed of Panax ginseng, Ophiopogon japonicus, and Schisandra chinensis (8). It has been applied clinically to treat heart failure (HF) as an important supplementary drug and is included in the latest Chinese Health Insurance Catalog (9). YQFM significantly improves cardiac function and related indicators and relieves cardiac load and related symptoms among HF patients (10). Pharmacological studies have demonstrated that YQFM can inhibit myocardial remodeling, attenuate cardiomyocyte hypertrophy and apoptosis, and improve the cardiomyocytes’ energy metabolism, which is achieved by various signaling pathways (11).

We are conducting a large sample, randomized, double-blind, placebo-controlled trial (AUGUST-AHF RCT study) to evaluate the YQFM effect on the 90-day mortality or readmission rate in AHF patients (8). However, restrictive eligibility criteria from a randomized clinical trial (RCT) may raise concerns about the generalizability of the results to under-represented groups or complex patients with multimorbidity, as seen in routine clinical practice (12). A tight regulatory framework may be appropriate for early-phase RCT, but its ubiquitous application to clinical trials may stifle the ability to test the YQFM. In some published studies, RCT results are inconsistent when the treatment or drugs are transferred to clinical practice (13, 14). Thus, observational data from a real-world study may be needed to address some AUGUST-AHF RCT study limitations, providing an effectiveness evaluation applicable to a broad population in routine clinical practice.

Here, we intend to conduct the AUGUST-AHF cohort study (Figure 1), which aims to (1) assess the effectiveness of YQFM on the 90-day mortality or readmission rate in patients with AHF in a real-world setting; (2) compare the results of our study with AUGUST-AHF RCT study; (3) determine the representativeness of the AUGUST-AHF RCT study populations to real-world patients, and describe differences in patients’ characteristics who met the RCT eligibility and those not in AUGUST-AHF cohort study.

**FIGURE 1 F1:**
[figure not shown]
Overview of study objectives and flow diagram of AUGUST-AHF cohort study. **(A)** Out of this study. Of the total population of AHF people with yiqi fumai lyophilized injection (YQFM), only a subset are included in randomized controlled trials (RCT), based on the RCT inclusion/exclusion criteria. For this study, the specific RCT of interest is the AUGUST-AHF RCT study, an ongoing RCT which also performed by our team, evaluating the efficacy of YQFM on long-term prognosis. The RCT generates results that inform clinical practice, and the anonymized raw data for the study will be made available to us. **(B)** Work will be performed in this study (AUGUST-AHF cohort study). This cohort study will comprise patients with AHF, and they will be divided into unexposed and exposed groups according to whether are taking YQFM in real clinical practice. The primary outcome will be a composite of 90-day all-cause mortality or readmission for heart failure, which is the same as AUGUST-AHF RCT study. During 180- day follow-up, we will provide patients with smart watches to monitor their body weight, blood pressure, and heart rate. Smartphone-based clinical reporting applications will also be used to manage patients. Objective 1: thorough our cohort study, assess the effectiveness of YQFM on the 90-day mortality or readmission rate in patients with AHF in real-world setting. Objective 2 compare the result of our study with AUGUST-AHF RCT study. Objective 3 determine the representativeness of the AUGUST-AHF RCT study populations to real-world patients, and describe differences in the characteristics of patients who met the RCT eligibility and those not in AUGUST-AHF cohort study. AHF, acute heart failure; YQFM, yiqi fumai lyophilized injection; RCT, randomized controlled trial.

## 2. Materials and methods

### 2.1. Study design

This prospective, multicenter cohort study will be conducted at 50 secondary and tertiary hospitals. Approval for the study has been obtained from the Ethical Committee of Dongzhimen Hospital (approval No. 2022DZMEC-327-02). The study has been registered at ClinicalTrials.gov (NCT05586048).

Outcome	Primary outcome: 90-day all-cause mortality or HF readmission Secondary outcomes: 180-day all-cause death or HF readmission, length of hospital stay, 90-day cardiac-specific death, MACE, dyspnoea via VAS, dyspnoea via Likert 7-point scale, NYHA function class, MLHFQ scale, MMAS-8, heart rate at follow-up	Primary outcome: 90-day all-cause mortality or HF readmission Secondary outcomes: 180-day all-cause mortality or HF readmission rate, length of hospital stay, 90-day cardiac-specific death, MACE, dyspnoea via VAS score, dyspnoea via Likert 7-point scale, NYHA functional class, WHF, MLHFQ scale, intravenous diuretics, NT-proBNP
Follow-up	180 days	180 days
Study design	Cohort study	RCT

HF, heart failure; MACE, major cardiovascular adverse event; VAS, dyspnoea via visual analog scale; MLHFQ, minnesota living with heart failure quality of life; MMAS-8, morisky medication adherence scale; RCT, randomized controlled trial.

### 2.4. Outcomes

The primary outcome is a composite of 90-day all-cause mortality or readmission for HF. The secondary outcomes are 180-day all-cause death or HF readmission, cardiac-specific death, major cardiovascular adverse event (MACE), length of hospital stay, dyspnoea by visual analog scale (VAS), dyspnoea by Likert 7-point scale, New York heart association (NYHA) cardiac function classification, Minnesota Living with Heart Failure Quality of Life (MLHFQ) scale, and Morisky Medication Adherence Scale (MMAS)-8. The cardiac-specific death is defined as death due to myocardial infarction (MI), worsening heart failure, death due to cardiovascular procedures, or other cardiovascular causes. MACE is defined as any of the following: death, MI, stroke, hospitalization because of HF, and revascularization, which includes percutaneous coronary intervention and coronary artery bypass grafting.

### 2.5. Study assessment

Researchers will assess patients daily during their hospitalization until their discharge and at the follow-up (details shown in Table 2). After patients have been enrolled in this study, researchers will examine their eligibility for the AUGST-AHF RCT study. The use of YQFM will be evaluated based on the daily medication record. The MACE endpoints and cardiac-specific death will be assessed and determined by the endpoint committee. VAS and 7-point Likert scale will be used to assess dyspnea by patient self-report, and the two scales will be measured at approximately the same time in patients’ supine position to ensure consistency. The MLHFQ scale consists of 21 questions and has been widely used to assess HF patients’ life quality (17). The Chinese version of MMAS of eight items has been extensively validated in China (18). It shows reliability and validity for HF patients (19), which would be a suitable tool for our study to assess patients’ medication adherence. Adverse events (AEs) will be monitored until Day 10 or until patients are discharged and significant AEs until Day 180.

**TABLE 2 T2:** The schedule of assessment and data collection.

	Baseline	During the patient’s hospitalization^1^										Follow-up			
**Time point**	**Day 0**	**Day 1**	**Day 2**	**Day 3**	**Day 4**	**Day 5**	**Day 6**	**Day 7**	**Day 8**	**Day 9**	**Day 10**	**Day 30**	**Day 60**	**Day 90**	**Day 180**
**Screening procedures**															
Eligibility screen	X														
Informed consort	X														
**Data collection and assessments**															
Basic information^2^	X														
AUGUST-AHF eligibility judgement^3^	X														
YQFM usage		X	X	X	X	X	X	X	X	X	X				
Physical examination*	X	X	X	X	X	X	X	X	X	X	X				
Weight*	X	X	X	X	X	X	X	X	X	X	X				
Total intravenous diuretics*	X	X	X	X	X	X	X	X	X	X	X				
Laboratory inspection*	X										X				
Myocardial injury biomarker*	X														
ECG*	X										X				
Echocardiogram*	X														
BNP or NT-proBNP*	X														
NYHA cardiac function classification	X										X			X	
Dyspnoea via VAS	X	X	X	X	X	X	X	X	X	X	X				
Dyspnoea via Likert 7-point comparator scale	X	X	X	X	X	X	X	X	X	X	X				
MLHFQ scale	X										X	X	X	X	X
Length of hospital and CCU stay											X				
Readmission for HF												X	X	X	X
All-cause death												X	X	X	X
Heart rate												X	X	X	X
MMAS-8												X	X	X	X
MACE												X	X	X	X
Adverse and serious adverse events	X	X	X	X	X	X	X	X	X	X	X	X	X	X	X
Medications^4^	X	X	X	X	X	X	X	X	X	X	X	X	X	X	X

^1^If the hospital stay is less than 10 days, the necessary assessment will be completed before discharge. If the patient stays for more than 10 days, the use of Yiqi Fumai will be completed daily in the remaining hospital stay, and the MLHFQ scale will be additionally completed at discharge. ^2^Basic information concludes patient’s demographic information, comorbidity, disease history, alcohol and tobacco history, allergy history, and influenza vaccination history. ^3^AUGUST-AHF eligibility determination: The patient will be evaluated by the researchers according to the eligibility of the AUGST-AHF to determine whether the patient met the criteria. ^4^Medications will be recorded at baseline, during hospitalization, and follow-up period, especially drugs with clear beneficial effects in patients with heart failure, such as SGLT2, ARNI, ACEI, ARB, and β-blocker. *Non-required items, which will be obtained from electronic medical record if recorded. YQFM, Yiqi Fumai lyophilized injection; ECG, electrocardiogram; NYHA, New York heart association; MLHFQ, minnesota living with heart failure quality of life; CCU, coronary care unit; MMAS, morisky medication adherence scale; MACE, major cardiovascular adverse event; SGLT2, sodium-glucose co-transporter 2; ARNI, angiotensin receptor-neprilysin inhibitor; ACEI, angiotensin-converting enzyme inhibitors; ARB, angiotensin receptor blockers.

### 2.6. Data collection and management

#### 2.6.1. Data collection during hospitalization

Identities of patients will be encoded with numbers to protect their privacy. At enrolment, patients’ basic information will be obtained, including demographic information, disease history, alcohol, cigarette use, allergy history, and influenza vaccine history. Moreover, information on laboratory examination, imaging examination, and medications will be collected. The laboratory inspection includes biochemistry, hematology, and routine urine analysis. The medication information, including the name, the dosage, and the duration of the medication use, will be recorded throughout the study. More details about data collection across time points are shown in Table 2.

#### 2.6.2. Follow-up

Following enrolment, patients will be monitored for a minimum of 180 days, with visits occurring at 30, 60, 90, and 180 days. During follow-up, we will use a smartphone-based clinical reporting application (app) to manage patients. Patients will fill out the MLHFQ and MMAS-8 scales online by this app. Before discharge, the doctor will explain the details of the app’s scales to patients and their relatives until they fully understand. Concurrently, the app will display essential discharge instructions and details. Within seven days of each visit time point (30, 60, 90, and 180 days), an independent investigator will confirm survival status, HF readmission, NYHA cardiac function classification, MACE, and AEs of patients by telephone or outpatient, and remind patients to complete the app questionnaire in the app. We will provide patients with smartwatches and ask them to wear these smartwatches during follow-up, which could monitor their body weight, BP, and heart rate. The records will be automatically uploaded to the app through Bluetooth. All data will be sent over the internet to a back-end infrastructure on secure servers. Moreover, this specially designed app gives researchers secure online access to scale information and patients’ vital-sign readings.

#### 2.6.3. Data management

All data will be collected by Case Report Form (CRF) of a paper version and then transcribed to electronic data capture (EDC) system. To ensure data accuracy, data entry personnel will receive the necessary training and perform entry while checking for any suspicious parameters. The data will be monitored regularly for quality control by a data management team. Team members will periodically check the validity and logicality of the data through the EDC system and send electronic queries to the fillers in case of any questions until the data is confirmed to be correct. The team will also organize regular visits to centers and check the paper consistency and electronic CRFs.

### 2.7. Sample size

Based on the results of previous observational studies, the composite outcome of 90-day all-cause mortality or readmission for HF was approximately 25% among patients who received conventional therapy for acute heart failure (20, 21). We assumed that the composite rate of those who combined with YQFM in clinical practice is 18%. Setting a significance level of two-sided alpha level of 0.05 and 10% of the loss to follow-up, 1,200 patients would be enough to detect the composite outcome with 80% power.

### 2.8. Statistical analysis

The baseline characteristic and observational data will be expressed as means ± standard deviation, medians, or percentages, and performed an independent t-test, Mann-Whitney U test, or Chi-square test/Fisher’s exact test, depending on the distribution.

Cox proportional-hazards regression models will be used to estimate the association between YQFM use and the primary outcome. An initial multivariable Cox regression model will include demographic factors, clinical factors, laboratory tests, and medications.

The primary analysis will use propensity-score matching methods to balance the differences in baseline variables between treatment cohorts. The individual propensities for receipt of YQFM treatment will be estimated with the use of a multivariable logistic regression model that include the same covariates as the Cox regression model. In the propensity-score matching analysis, the nearest-neighbor method will be applied to create a matched control sample. All variables will include in the propensity score model reflected knowledge available at baseline. Missing baseline variables will be handled by multiple imputation by chained equations using the other variables available. To verify the covariate balancing after the propensity score matching, the standardized mean difference (SMD) will be calculated with a threshold of 10% designated to indicate clinically meaningful imbalance (22). Kaplan-Meier curves and Cox models that use the propensity-score matching will be reported. A sensitivity analysis for unobserved confounding will be performed by using the Rosenbaum’s method to assess the robustness of findings due to hidden bias (23).

We will compare our findings with the AUGUST-AHF RCT study to determine whether the results, particularly the primary outcome, are compatible between the two. The proportion of patients who met the eligibility requirements for the AUGUST-AHF RCT study will be computed. Differences in baseline characteristics between those who met the RCT eligibility and those who did not will also be tested by the statistical methods described above.

We will perform an interim analysis when 33% of total patients (N = 400) have completed the 90-day follow-up. The interim analysis will be performed by independent statisticians, and we may adjust the course of the subsequent study or revise the study protocol based on the analysis results.

All statistical analyses were performed with the R statistical package version 4.0.2 (R Foundation for Statistical Computing, https://www.R-project.org/). Furthermore, two-tailed p < 0.05 was considered statistically significant.

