#### 3.2.2. Study design rationale

In our study, we will apply a broader eligibility criterion and nearly the same outcome measures as the AUGUST-AHF RCT study (shown in Tables 1, 2). The study results will represent the long-term effectiveness of YQFM in a real-world setting.

Furthermore, we will compare the population and results of our study with the AUGUST-AHF RCT study. Complex patients with multimorbidity or a history of specific treatments, like heart transplantation, will be excluded from the AUGUST-AHF RCT investigation, raising concerns regarding the trial’s generalizability and the unknown benefit and risk of Yiqi Fumai Lyophilized Injection for this group. In our study, we specifically set up an assessment to determine whether patients are eligible for the AUGST-AHF RCT study. By comparing the populations of the two studies, we could determine the representativeness of the AUGUST-AHF RCT study populations to real-world patients and describe differences in the characteristics of patients who met the RCT eligibility criteria and those who did not participate in a real-world setting, something that is rarely mentioned in existing studies. Those who do not meet the AUGUST-AHF eligibility criteria will be analyzed separately to obtain efficacy in an underrepresented population.

Some studies have demonstrated that the outcomes of patients in clinical trials differ from those in real-world settings, with lower survival rates and a higher incidence of AEs (13, 14). The results of our study will be compared with AUGUST-AHF to verify whether this condition also exists in HF patients and to analyze its possible causes. The outcome measures are largely the same between the two studies, facilitating data comparability. Furthermore, differences in compliance between trial and non-trial patients have been cited as an important reason for differences in results (39). Thus, we will include compliance analysis as an important part of the study to explore the differences in compliance between patients in and out of clinical trials and their impact on clinical outcomes. The study outcomes will aid patients, physicians, and policymakers in selecting the optimal treatment options for all patient subgroups. The method could potentially serve as a model for utilizing RCT-validated data in routine clinical practice.

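### The primary matched analysis estimates the effect in YQFM recipients who can be matched, whereas the article claims effectiveness for a broad AHF population; the two can differ in either direction.

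*Protocol article*

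**What the plan says.** **The analysis.** Section 2.8 states: "The primary analysis will use propensity-score matching methods to balance the differences in baseline variables between treatment cohorts". For the matching step, "the nearest-neighbor method will be applied to create a matched control sample". Kaplan-Meier curves and Cox models are then reported on the matched data. Ahead of this the section names a model without matching: "An initial multivariable Cox regression model will include demographic factors, clinical factors, laboratory tests, and medications".

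**The claimed population.** Objective 1 in the Introduction is to "assess the effectiveness of YQFM on the 90-day mortality or readmission rate in patients with AHF in a real-world setting". The rationale there presents the cohort as "providing an effectiveness evaluation applicable to a broad population in routine clinical practice". Section 3.2.2 adds: "The study results will represent the long-term effectiveness of YQFM in a real-world setting". It also expects the results to help with "selecting the optimal treatment options for all patient subgroups".

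**Under-represented patients.** Section 3.2.2 plans an analysis of their own: "Those who do not meet the AUGUST-AHF eligibility criteria will be analyzed separately to obtain efficacy in an underrepresented population". Section 2.8 will compute the RCT-eligible proportion and compare baseline characteristics of eligible and ineligible patients.

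**Exposure.** Section 2.3 leaves treatment to the physician's discretion and the patient's preference. The article gives no expected share of patients exposed, overall or by patient type.

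**The concern.** Building a control sample around the recipients fixes whose effect is estimated: that of treated patients, or of those among them who find a match. Non-recipients who resemble no recipient contribute nothing. The case mix of the primary analysis is therefore set by who was given YQFM, not by who was enrolled.

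That matters here because the cohort exists to go beyond the RCT population. Section 3.2.2 calls the benefit and risk in complex patients unknown, so a uniform effect cannot be taken for granted. With uptake left to clinical judgement, equal uptake across patient types cannot be taken for granted either. If both vary, the primary hazard ratio is not the effect in the enrolled cohort, yet Objective 1 would be read that way. Objective 2 compares the two studies mainly on the primary outcome, so the same shift in case mix enters that comparison. The limitations paragraph in section 3.2.2 credits propensity methods with avoiding selection bias and does not say that matching itself selects the analysed sample.

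**Working it through.** **1. The plan's own figure.** Section 2.7 gives 25% vs 18%, two-sided alpha 0.05, 80% power and 10% loss. With pooled variance and 1:1 groups:

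n per group = [1.960·√(2·0.215·0.785) + 0.842·√(0.25·0.75 + 0.18·0.82)]² / 0.07² = 539.5, rounded up to 540.

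Total 1,080; 1,080/0.9 = 1,200. The stated size reproduces, so the point does not rest on a sample-size error.

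**2. Formulas.** Two patient types, RCT-eligible and RCT-ineligible. Let s be the eligible share of the cohort, e1 and e0 the YQFM uptake in eligible and ineligible patients, and RD1 and RD0 the 90-day risk differences.

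- Eligible share among recipients: w = s·e1 / [s·e1 + (1−s)·e0]
- Effect in recipients: w·RD1 + (1−w)·RD0
- Effect in the enrolled cohort: s·RD1 + (1−s)·RD0

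These take every recipient as matched and balance as perfect. The two effects coincide if e1 = e0 or RD1 = RD0.

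**3. First illustration.** From the document: 25% risk without YQFM (section 2.7), applied to both types. Assumed: s = 0.5, hazard ratio 0.6 in eligible and 1.0 in ineligible patients. Then the eligible risk with YQFM is 1 − 0.75^0.6 = 15.9%, RD1 = −9.1 points, RD0 = 0. The cohort effect is 0.5 × (−9.1) = −4.6 points.

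| Assumed uptake, eligible / ineligible | Ineligible share of recipients | Effect in recipients | Against cohort (−4.6) |
|---|---|---|---|
| 50% / 20% | 0.10/0.35 = 28.6% | 0.714 × (−9.1) = −6.5 | 0.714/0.5: 43% larger |
| 45% / 35% | 0.175/0.40 = 43.75% | 0.5625 × (−9.1) = −5.1 | 0.5625/0.5: 12.5% larger |
| equal | 50% | −4.6 | none |
| 20% / 50% | 0.25/0.35 = 71.4% | 0.286 × (−9.1) = −2.6 | 0.286/0.5: 43% smaller |

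On the planned scale, taking HR ≈ ln(1 − risk with YQFM)/ln(0.75):

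- cohort: risk 20.4%, HR 0.79
- recipients, 50%/20% uptake: risk 18.5%, HR 0.71
- recipients, 20%/50% uptake: risk 22.4%, HR 0.88

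**4. Second illustration, other assumed inputs.** s = 0.6; uptake 60%/20%; control risks 22% and 29.5% (average 0.6 × 22 + 0.4 × 29.5 = 25%); risk ratio 0.72 in eligible and 1.0 in ineligible patients. RD1 = 22 × (−0.28) = −6.16 points, RD0 = 0, w = 0.36/0.44 = 0.818.

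- Recipients: 0.818 × (−6.16) = −5.0 points
- Cohort: 0.6 × (−6.16) = −3.7 points, so the recipients' effect is about 36% larger
- Ineligible patients are 18% of recipients against 40% of the cohort
- With 50% uptake in both types: −3.7 points in each, no gap

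With a common risk ratio of 0.72, RD0 = 29.5 × (−0.28) = −8.26 and the figures are −6.5 and −7.0 points. That difference comes from baseline risk alone; the risk ratio is the same in both populations. Whether there is a gap therefore depends on the effect scale as well.

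**The case against.** **The effect in treated patients is a legitimate target.** Patients who receive YQFM in routine care are a real-world population, the cohort has a single exclusion criterion (Table 1), and no sentence promises an average over every enrolled patient. This stands as far as it goes: the choice of target is not an error. But the article does not declare it, and the Introduction and section 3.2.2 word the claim more widely.

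**Under-represented patients have their own analysis, and a full-cohort Cox model is planned.** Both are true, and both soften the point. Neither is primary. The separate analysis describes RCT-ineligible patients and does not turn the primary hazard ratio into a cohort-wide one. The multivariable model includes patients of all types, but it yields a covariate-conditional hazard ratio with one common coefficient, not an effect averaged over the cohort's case mix.

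**Estimand wording and weighted models often sit in the analysis plan.** Fair, and the unstated matching ratio, caliper and replacement rule are not counted against the article. The point rests on two things it does state: a recipient-based primary analysis and a broad-population claim.

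**Stronger readings the documents do not support.**

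- A reader might infer that under-represented patients fall out of the main answer. Recipients of every type stay in if they can be matched; even with 50%/20% uptake, ineligible patients are 28.6% of recipients.
- A reader might infer that complex patients seldom receive YQFM. No sentence says so. Table 1 excludes patients with YQFM allergy from the RCT only, which suggests unequal uptake in that one group, but the article gives no uptake figures.
- A reader might infer that agreement with the RCT is built in. That needs uptake to favour RCT-like patients, which is unknown, and a case mix nearer the RCT's would also make the comparison more like-for-like.

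**Conclusion.** The mismatch is real and modest in kind: the primary analysis answers for matched YQFM recipients, while the stated claim is for a broad AHF population. It has numerical consequences only if uptake and effect both vary by patient type, on the effect scale used. The article gives no data on either, so size and direction cannot be determined. Under the assumed inputs the gap runs from none, through 12.5%, to about 40% in either direction. The upper figures need a 2.5- to 3-fold difference in uptake together with no effect at all in one patient type, so they mark a range and are not evidence of bias. In particular, the material does not show that the primary result will overstate the benefit: reversing the uptake pattern reverses the sign of the gap. It is worth correcting before results are seen, because it governs what Objectives 1 and 2 may conclude.

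**What to change.** In section 2.8:

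1. Keep the matched Cox model as primary and state that it estimates the effect in YQFM recipients who can be matched.
2. Pre-specify, as supportive, a Cox model in all enrolled patients weighted by the same propensity score, with an overlap check by patient type. If weights are truncated, give the rule and say that truncation moves the estimate away from the full-cohort target.
3. Show the RCT-eligible share and the key baseline variables of the matched sample beside those of the full cohort. The cohort figures are already planned; only the matched column is new.
4. If the matched and weighted estimates differ by more than a margin set beforehand, limit the Objective 1 conclusion and the comparison with the RCT to patients like those who receive YQFM.

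Cost: plan wording, one further model and one table column, with no new data or patients. The weighted interval may be wider where few patients of a type receive YQFM. Where almost none do, weighting cannot supply the missing information, and the overlap check should say so.
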